## Abstract

**Background:**

Major depression will become the second most important cause of disability in 2020. Computerized cognitive-behaviour therapy could be an efficacious and cost-effective option for its treatment. No studies on cost-effectiveness of low intensity vs self-guided psychotherapy has been carried out. The aim of this study is to assess the efficacy of low intensity vs self-guided psychotherapy for major depression in the Spanish health system.

**Methods:**

The study is made up of 3 phases: 1.- Development of a computerized cognitive-behaviour therapy for depression tailored to Spanish health system. 2.- Multicenter controlled, randomized study: A sample (N=450 patients) with mild/moderate depression recruited in primary care. They should have internet availability at home, not receive any previous psychological treatment, and not suffer from any other severe somatic or psychological disorder. They will be allocated to one of 3 treatments: a) Low intensity Internet-delivered psychotherapy + improved treatment as usual (ITAU) by GP, b) Self-guided Internet-delivered psychotherapy + ITAU or c) ITAU. Patients will be diagnosed with MINI psychiatric interview. Main outcome variable will be Beck Depression Inventory. It will be also administered EuroQol 5D (quality of life) and Client Service Receipt Inventory (consume of health and social services). Patients will be assessed at baseline, 3 and 12 months. An intention to treat and a per protocol analysis will be performed.

**Discussion:**

The comparisons between low intensity and self-guided are infrequent, and also a comparative economic evaluation between them and compared with usual treatment in primary. The strength of the study is that it is a multicenter, randomized, controlled trial of low intensity and self-guided Internet-delivered psychotherapy for depression in primary care, being the treatment completely integrated in primary care setting.

**Trial registration:**

Clinical Trials NCT01611818

## Background

Major depression is a prevalent mental disorder associated with significant disability and economic costs [1]. In this sense, it is known that 25% of all human beings will suffer from a depression at any moment over their lives [2] and, according to the World Health Organization [3], depression will become the second most important cause of disability in 2020. From the perspective of the health system, 25-35% of the patients attending primary care settings suffer from a psychiatric disorder and more than 80% of them are depression and/or anxiety [4]. This percentage is higher at the Spanish Primary Care where 45% of the patients have had a mental disorder during their life, with 31% experiencing a mental disorder in the past 12 months [5]. Almost 30% attendees reported a lifetime history of major depressive disorder, with 9.6% experiencing major depression in the past year. In most countries, general practitioners refer only 5-10% of the patients with psychiatric disorders to specialized services [4] and, despite of that, mental health services are collapsed all over the world.

Major depression can be treated effectively using antidepressants, but relapse is high following cessation, and many patients prefer psychological therapies [6], which are as effective as pharmacological treatment [7]. Although evidence-based treatments exist, rates of treatment seeking are low, and many patients with depression do not receive adequate management, being the main barriers the limited availability of trained clinicians with consequent long waiting lists, direct and indirect costs of treatment, stigma, and difficulty attending therapy during business hours [8]. These reasons, expected to get worse in the future, had convinced international health authorities to search for new cost-effective treatment alternatives for depression [9].

It has been defined “Computer-delivered psychotherapy” (CDP) as any psychotherapy program that uses patients’ inputs to take decisions regarding treatment [10-12]. This excludes videoconferences, self-help programs exclusively based on bibliotherapy, chats, help groups, etc. Patients receive therapy using their computers at home and the sessions are usually short (20–30 min.), on a weekly basis and the treatment lasts 3–6 months [10-12]. At this moment, there exist evidence of the effectiveness of CDP in depression [13], anxiety [14], and other psychiatric disorders such as alcohol abuse, psychosomatic disorders [15] or even pain [16]. Recently, cost-effectiveness studies on CDP have been published with satisfactory results [17-20]. The results has lead to British NICE to support the use of a computer-delivered psychotherapy program for the treatment of depression ("Beating the Blues") to be widely used by the patients of the British National Health Service [11,21]. Other studies show that CDP is so effective that it should be used not only at primary care level, but even in mental health services. In these specialized settings, it would be recommended as a self-help first step for depression and anxiety, before being attended by a psychologist or psychiatrist [22]. Recently, other CDP programs without the presence of a psychotherapist, such as "Blues Begone", have been evaluated with adequate effectiveness not only in randomized controlled trials [23] but in naturalistic studies as well [24].

Internet-delivered psychotherapy (iPT) is a form of CDP delivered by internet. According to NICE [21], iPT programs are highly structured and comprises systematically presented online lessons, homework, and supplementary resources. Programs may be entirely self-guided, or patients may receive therapist contact via asynchronous e-mails or synchronous online chat or telephone calls. Depending on the time devoted by the psychotherapist to the patient, iPT programs can be broadly divided into low-intensity (<3 h) and high-intensity iPT (>3 h of therapist time in total) [25]. Although an Internet connection and basic computer hardware are required, some of the advantages of iPT include convenience, treatment fidelity, and accessibility. That is, patients and therapists may logon to the program at anytime, every patient receives exactly the same materials, and barriers relating to stigma, geography and limited therapist resources are minimized [21].

While there is consensus about the effectiveness of iPT for major depression, it is still unknown how these interventions work and for whom they work. This holds true for other types of intervention as well, despite some exploratory studies on this subject [26,27]. For this reason, it is relevant to examine potential mediating and moderating variables that explain the effect of these treatments. Another key challenge is how to successfully adapt and disseminate iPT programs developed and evaluated in a research environment to the heterogeneous health services of developed and developing countries. One recent example is a program that was effective in reducing depressive symptoms in an RCT [28], but which did not improve treatment outcomes when added to treatment as usual in primary care settings [29]. Regarding this, it is recommendable to develop studies in which iPT be integrated within usual primary care services. The efficacy and reliability of iPT have been demonstrated for depression in different countries and different languages, especially English, but as far as we know, there is no validated internet delivery program in Spanish. Since Spanish is, after English one of the most used languages in the world, it seems highly relevant that an online treatment program in Spanish for depressive patients in primary care could be tested. Finally, an unresearched question is the attitude towards iPT not only of the patients that receive it, but of the health professionals (both general practitioners and psychologists/psychiatrists) and stakeholders. Curiously, the attitudes of professionals are usually more negative than patients’ [30,31], but both are moderated by their experience with iPT [32,33]. To better tailor the programs to the environment in which they are intended to be used and about the acceptability to stakeholders, in order to facilitate the integration of these programs into the health system, qualitative studies to identify attitudes and barriers are systematically recommended.

The main objective of this study will be to compare the effectiveness of a low intensity vs. a self-guided Internet-delivered psychotherapy program compared with ITAU for the treatment of major depression in primary care in Spain, with a multicenter, randomized, controlled trial. The secondary objective will be the cost-effectiveness of those programs, to identify the patients that most benefit of these programs and to examine the potential mediators and moderators. In this article we describe the design of the study.

## Methods

### Study design

This study is a multicenter, randomized controlled trial. Subjects will be randomized into three groups: a) Low intensity Internet-delivered psychotherapy, b) Self-guided Internet-delivered psychotherapy and c) improved Treatment as Usual (ITAU) group in primary care. The evaluation of the treatment outcomes will be performed at patient level and they will be assessed individually.

### Setting and study sample

Patients will be recruited from primary health care centers of the three Spanish regions participating in the study. Patients will be recruited by general practitioners (GPs) working in these primary care centers until the required sample is completed, without a quota of patients assigned for each centre. Patients considered for inclusion are those aged 18–65 years, able to understand and read Spanish, with moderate or mild major depression, duration of symptoms longer than 2 weeks, access to Internet at home and having an email address. Exclusion criteria includes any psychological treatment during last year, severe psychiatric disorder in Axis I (alcohol/substances abuse or dependence, psychotic disorders or dementia) and patients with severe depression (indicated by a Beck-II score of 29 or higher) who will be advised to consult their GP. Receiving pharmacological treatment with antidepressants is not an exclusion criteria meanwhile, during the study period, treatment will not be modified or increased (decrease of pharmacological treatment is accepted). Diagnosis of major depression will be carried out with MINI International Neuropsychiatric Interview + scoring of moderate or mild depression using Beck Depression Inventory II. Cut-off point for this questionnaire is: 0–13: minimal depression; 14–19: mild depression; 20–28: moderate depression; 29–63: severe depression [34,35].

### Sample size

The sample size of this study was based on the expected difference on the primary outcome variable, i.e. depressive symptoms, between the intervention groups and the Treatment as Usual group at post-test. Based on a power of 0.80 in a one-tailed test, an alpha of 0.05, we need 100 subjects in each condition to show an effect-size of 0.40.

Therefore, the total sample size was determined at 300. This sample size also allows calculating clinically significant difference in the main outcome variable, Beck Depression Inventory II. Based on previous studies [36], this difference has been placed at 5 points. It allows changing scoring from normality to mild depression or from mild to moderate depression. Taking account an expected withdrawal rate of 30% according to previous studies [9-14], a sample size of 450 patients (150 by arm) was calculated. The three participating health centers will select 150 patients with cluster randomization to allocate one third in each of the three arms.

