### Analysis strategy

#### Analysis of clinical efficacy

The analysis will be per intent to treat and will follow CONSORT recommendations [54]. First, the three groups will be compared in order to verify that there are no significant differences among them at baseline to confirm they are comparable after randomization.

For comparisons, the ANOVA for continuous variables and the Chi-squared test for categorical variables will be used. Non-parametric tests may also be used. To confirm main hypothesis, an analysis of variance (ANOVA) of repeated measures, including all the assessments over the time, will be carried. The main outcome, scoring of BDI-II, will be used as continuous variable. Models will include adjustment by baseline value of BDI-II and any other variable that show differences among groups at baseline. Possible interactions Group × Time will be assessed using Mixed Factorial Anova (3 × 4: 3 groups by 4 temporal moments). Other linear regression models will be used to compare differences in BDI-II scoring among groups for each assessment over the time compared to baseline. Similar analysis will be carried out for secondary outcomes. For missing values a sensitivity analysis will be used to estimate the effect of missing values. Those valued will be replaced using different systems such as last registered values and imputations.

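### The one-tailed inputs of the sample-size statement give 78 per arm; the stated 100 is the two-sided result, which also fits the planned ANOVA

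*Protocol article*

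**What the plan says.** The Sample size section bases the calculation on the difference in depressive symptoms "between the intervention groups and the Treatment as Usual group at post-test". It then states: "Based on a power of 0.80 in a one-tailed test, an alpha of 0.05, we need 100 subjects in each condition". The effect size behind this figure is given as 0.40. That leads to 300 in total. An expected withdrawal of 30% is applied afterwards, leading to 450 patients, 150 per arm.

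The section Analysis of clinical efficacy says that, to confirm the main hypothesis, "an analysis of variance (ANOVA) of repeated measures, including all the assessments over the time, will be carried". It adds a 3 × 4 mixed factorial ANOVA for the group-by-time interaction, and linear regression models for each assessment. It mentions no one-tailed test.

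The abstract words the aim as a comparison of the two programmes: "The aim of this study is to assess the efficacy of low intensity vs self-guided psychotherapy for major depression". The main objective at the end of the Background section names both programmes and also the comparison with ITAU.

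**The concern.** A sample-size sentence should let a reader put the inputs into the standard formula and recover the answer. This one does not. Either the sidedness or the figure of 100 is wrong, and the two readings imply different significance thresholds for the comparison that the trial was sized on.

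The label is also out of step with the analysis. The F tests of a three-group repeated-measures or mixed ANOVA respond to differences in any direction, so a one-tailed calculation does not describe the test that will be run. A reader cannot tell from the text which threshold the stated power of 0.80 belongs to. Nor does the text say that the figure applies to one comparison with ITAU at a time, and not to the comparison of the two programmes that the abstract puts first.

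**Working it through.** **Inputs, all from the Sample size section**

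- Sidedness and power: "Based on a power of 0.80 in a one-tailed test".
- Significance level: "an alpha of 0.05".
- Effect size 0.40. The metric is not named. It is read here as a standardized mean difference d, because the text describes a difference between an intervention group and usual care.
- Equal allocation to three arms; 100 evaluable per arm stated.
- Withdrawal of 30%, applied after the 100.

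**Formula**, for two equal groups: n per arm = 2(z_α + z_β)² / d², with z_β = 0.842 for power 0.80 and d² = 0.16.

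**Step 1. Does the plan's figure reproduce from its own inputs?**

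One-sided 0.05: 2(1.645 + 0.842)² / 0.16 = 77.3, so 78 per arm. The t-based solution is 77.97, also 78. The total would be 3 × 78 = 234, against the stated 300. The stated figure exceeds the computed one by 100 − 78 = 22 per arm, and 22/78 = 28%. This is not rounding.

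**Step 2. What does give 100?**

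Two-sided 0.05: 2(1.960 + 0.842)² / 0.16 = 98.1, so 99 per arm. The t-based solution is 99.08, so 100. This matches the plan.

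**Step 3. Other routes to 100**

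| Route | n per arm | Why it does not explain the text |
|---|---|---|
| One-sided 0.025 | 99 to 100 | The text states 0.05 and describes no split |
| Two-sided 0.025 | 119 (z), 121 (t) | Does not match |
| Omnibus three-group F test, means (0.4, 0.4, 0) | about 92 | Does not match |
| Omnibus three-group F test, means (0.4, 0.2, 0) | about 122 | Does not match |
| One-sided n inflated for a rank test | 82 to 91 | Does not match |
| One-sided n × 1.3 | 78 × 1.3 = 101.4, so 102 | Would count the withdrawal twice |

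**Step 4. Power that the stated numbers deliver at d = 0.40**

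At 100 per arm, d√(n/2) = 0.4 × √50 = 2.828.

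- One-sided: 2.828 − 1.645 = 1.183, power 0.88.
- Two-sided: 2.828 − 1.960 = 0.868, power 0.81 (t-based 0.80).

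After 30% withdrawal from 150, 150 × 0.70 = 105 per arm remain. Two-sided t-based power is then 0.82.

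**Step 5. Precision for low intensity versus self-guided**

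At 105 per arm, the half-width of the 95% confidence interval is 1.96 × √(2/105) = 0.27 SD.

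**The case against.** The strongest reply is that the slip is harmless. Against its own one-tailed inputs the trial is larger than needed (power 0.88), and against the two-sided reading it is sized correctly. No patient number, allocation or pairwise conclusion changes. This stands, and it sets the weight of the point: a correction to a design statement, not a flaw in the design. It does not rescue the sentence, whose inputs and answer still disagree.

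Three stronger readings are tempting, and the document supports none of them.

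- A reader might infer that either programme will be declared superior at one-sided 0.05, which is a two-sided p of up to 0.10. But the one-tailed label appears only in the sample-size calculation. The confirmatory ANOVA is non-directional, and the regression models have no stated sidedness. No such decision rule is written.
- A reader might infer that the overall error rate is uncontrolled, since two programmes share one control arm. The article states no multiplicity rule, but that is commonly left to the statistical analysis plan, which is not shown. The article does not say whether pairwise tests would follow only a significant overall test, so no particular error rate can be attributed to it.
- A reader might infer that the trial is under-powered for its real question, low intensity versus self-guided. The abstract's wording is short; the full objective includes the comparison with ITAU, and the sample-size text openly sizes on that. The document gives no expected difference between the two programmes, so any power figure would rest on an assumed effect. What stands is only that this comparison was not sized.

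**Conclusion.** The sample-size statement is wrong as written. Its inputs lead to 78 per arm; the stated 100 belongs to a two-sided 0.05 test. The two-sided reading reproduces the plan's figure and agrees with the non-directional F tests of the planned analysis, so the likeliest error is the one-tailed label and not the number.

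This should be corrected, but it does not put the trial at risk: 100 evaluable per arm is enough for a single unadjusted comparison of either programme with ITAU. The conclusion assumes that 0.40 is a standardized mean difference, that arms are equal, and that withdrawal is 30% as stated. The mismatch with the analysis is shown for the ANOVA tests only.

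**What to change.** In the Sample size section:

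1. Replace one-tailed with two-tailed and keep 100, 300 and 450. Keeping the one-tailed label and changing the figure to 78 would make the arithmetic agree, but would leave the conflict with the ANOVA.
2. Say that 0.40 is a standardized mean difference, if that is what was meant.
3. Say that the figure gives power 0.80 at 100 per arm, and 0.82 at the 105 left after 30% withdrawal, for each single, unadjusted comparison of an intervention arm with ITAU at post-test.
4. Say that low intensity versus self-guided was not sized, and that it will be reported as an estimate with a 95% confidence interval (half-width about 0.27 SD at 105 per arm), so that a non-significant difference is not taken as equivalence.

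The cost is a few sentences. Recruitment, allocation and the planned models stay as they are.

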### Randomization, allocation and masking of study groups

Each patient will be allocated to either one of the three groups using a computer-generated random number sequence. We will use block allocation, with 3 blocks (one for each participating region) including 150 patients per block, with about 50 patients per arm. The allocation will be carried out by an independent person, belonging to REDIAPP (Primary Care Prevention and Health Promotion Research Network), who is not involved in the study. The method used to implement the random allocation sequence will be a central telephone. The sequence will be concealed until interventions are assigned. Patients will agree to participate before the random allocation and without knowing which treatment they will be allocated to. Study personnel conducting psychological assessments will be masked to participants' treatment conditions.

The researcher that administers baseline assessments will be unaware of the treatment group to which the patient belongs to. This researcher will be different from the one that administer the questionnaires over the study. GPs will be also unaware, as long as possible, of the arm to which the patient has been randomized, since their treatment should be exclusively based on the recommendations of the guides for the treatment of depression. The flowchart of the study is summarized in Figure 1 (Insert by here).

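### The sample size section says clusters are randomised; the rest of the protocol randomises individual patients within three regions, and the unit of randomisation must be stated once

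*Protocol article*

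**What the plan says.** The sample size section sets the target at 450 patients, 150 per arm, and then says: "The three participating health centers will select 150 patients with cluster randomization to allocate one third in each of the three arms". It does not say what a cluster is and gives no ICC or design effect.

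The section on randomisation, allocation and masking says: "Each patient will be allocated to either one of the three groups using a computer-generated random number sequence". It continues: "We will use block allocation, with 3 blocks (one for each participating region) including 150 patients per block", with about 50 per arm. An independent person outside the study makes the allocation by central telephone, and the sequence stays concealed until assignment. The study design section also has subjects randomised and outcomes evaluated at patient level. The recruitment section places randomisation after consent, the eligibility interview and the baseline tests.

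The setting section recruits from primary care centres in three regions "without a quota of patients assigned for each centre". The analysis section plans a repeated-measures ANOVA, adjusted for baseline BDI-II and for any variable that differs between arms at baseline. It names neither a cluster term nor region.

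**The concern.** Two things conflict. The first is the unit of randomisation, a cluster in one section and a patient in the others. The second is the site level: three health centres with 150 patients each in one section, and three regions containing several centres with no quota per centre elsewhere.

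The unit of randomisation determines how allocation is concealed, how many patients are needed and how standard errors are computed. If clusters were randomised, a sample size without a design effect and an ANOVA without a cluster term would both be too optimistic. If patients are randomised, the sample size section misdescribes the trial, and whoever writes the allocation list, the analysis plan or a later appraisal could be misled.

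**Working it through.** **The plan's own figure.** Inputs from the sample size section: "Based on a power of 0.80 in a one-tailed test", alpha 0.05, effect size 0.40, 100 per arm. With n per arm = 2(z_alpha + z_power)² / d²:

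- one-sided 0.05: 2(1.645 + 0.842)² / 0.16 = 77.3, so 78 per arm;
- two-sided 0.05: 2(1.960 + 0.842)² / 0.16 = 98.1, so 99 per arm.

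The stated 100 matches the two-sided calculation, not the stated one-tailed test. That mismatch is a separate matter, but it is why power is shown both ways below. Both are formulae for individually randomised patients. With 30% withdrawal, 450 × 0.70 = 315 are analysed, or 105 per arm. Without clustering, power at d = 0.40 is then 0.89 one-sided and 0.83 two-sided (normal approximation).

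**Which unit fits the text?**

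| Feature | Cluster allocation | Individual allocation |
|---|---|---|
| Sample size section's label | yes | no |
| Each site's 150 split over all three arms (same sentence) | not if the site is the cluster | yes |
| Each patient allocated from a random sequence | no | yes |
| Allocation after consent and baseline tests, by central telephone | unusual | yes |
| GPs kept unaware of arm as far as possible | not if the GP is the cluster | yes |
| No ICC, design effect or cluster term | no | yes |

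Only the label points to clusters.

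**What if clusters were randomised after all?** The documents name no cluster, so the following are assumptions.

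- Clusters: the recruitment section estimates at least 10 GPs in each of three regions; take 30.
- Cluster size: 450 / 30 = 15 recruited; 15 × 0.70 = 10.5 analysed.
- ICC: none is given; take 0.01, 0.02 and 0.05.
- Design effect DE = 1 + (10.5 − 1) × ICC; effective n per arm = 105 / DE; power = Φ(0.40 × √(n/2) − z), with z = 1.645 one-sided or 1.960 two-sided.

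| ICC (assumed) | DE | Effective n per arm | Power, one-sided | Power, two-sided |
|---|---|---|---|---|
| none | 1 | 105 | 0.89 | 0.83 |
| 0.01 | 1.095 | 95.9 | 0.87 | 0.79 |
| 0.02 | 1.19 | 88.2 | 0.84 | 0.76 |
| 0.05 | 1.475 | 71.2 | 0.77 | 0.67 |

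**The block of 150.** The mean gap between the largest and smallest arm in a region (20,000 simulated sequences) was:

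| Patients so far | Block of 150 | Simple randomisation |
|---|---|---|
| 30 | 4.8 | 5.3 |
| 75 | 6.0 | 8.5 |
| 120 | 4.8 | 10.7 |
| 150 | 0 | 11.9 |

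The recruitment section expects 1 patient per GP per month for 12 months, so 10 GPs × 12 = 120 per region. At its unrounded rate, 12.3 × 0.25 × 0.25 = 0.77 per month, the figure is about 92. A block may therefore not fill, unless a region has more than the minimum of 10 GPs.

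**The case against.** The strongest reply is that the section meant to define allocation is clear. Sites do not allocate: an independent person does so by telephone, patient by patient, from a concealed sequence. One misplaced word in the sample size section is unlikely to change what happens. That is fair, and it is why the power figures above are conditional and do not describe the trial as most of the text defines it.

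Three stronger readings are tempting, and the documents do not support them.

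- *The health centres are the clusters.* With three centres this would mean one per arm, and arm would be fully confounded with centre. But the sentence splits each centre's 150 patients across all three arms, which cannot happen if the centre is the unit randomised.
- *The sample size is invalid.* It is not invalidated by clustering if patients are randomised. Even with GPs as clusters, the stated one-tailed test keeps more than 0.80 power up to an ICC of 0.02.
- *The block of 150 controls little.* A filled block balances its region exactly, and from the middle of recruitment it does clearly better than simple randomisation. The protocol expects only about 50 per arm, and long blocks make the next allocation hard to predict.

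It can also be said that model terms such as region are commonly left to the full protocol or analysis plan. That stands in so far as the omission is not an error; adding region is an improvement.

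**Conclusion.** The contradiction stands. The sample size section states a unit of randomisation, and a site level, that the rest of the protocol does not use. It concerns a core design feature and should be corrected, although the likeliest explanation is a misnomer for blocking by region and the damage is then confined to the text.

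If clusters were in fact intended, the planned power would not hold in general. Under the GP-cluster assumptions it falls below 0.80 two-sided at every ICC tried (0.79 to 0.67), and one-sided only at 0.05 (0.77). These figures rest on assumed clusters, cluster size and ICC, and on a normal approximation that ignores the limited number of clusters. Block size is a secondary point.

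**What to change.** In the last sentence of the sample size section, replace the three health centres with the three participating regions, and replace the cluster wording with *individual 1:1:1 randomisation stratified by region*. Use centre and region consistently throughout. This costs a wording change.

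Include region as a fixed factor in the BDI-II efficacy models, because allocation is blocked by region. This costs two degrees of freedom and needs no new data.

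If clusters really are to be randomised, the plan must instead define them, justify an ICC, inflate the sample size and use an analysis that accounts for clustering.

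Optional: within each region, use smaller permuted blocks of varying, concealed size, since a block of 150 may not fill and gives little balance early in recruitment. This needs a new allocation list before the first patient, and allocation becomes slightly more predictable.
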